### Participants

Patients will be individually and randomly assigned to one of the three parallel groups, initially in a 1:1:1 ratio, to an intervention group (rehabilitation gaming), active control group (entertainment gaming) or passive control group (no gaming) organized by the research study.

To be eligible for this study, participants must be Finnish speaking and reading adults between the ages of 18 and 65, who meet the eligibility criteria for people with traumatic brain injury (diagnostic criteria ICD-10, S06.X, T90.5) Participants must have been discharged from the neurologic treatment period due to traumatic brain injury over 12 months before the recruitment and must not have been actively participating in cognitive rehabilitation during the last 3 months. They must own a TV, a computer and have internet access at home, but must not be active digital gamers (5 hours or less a week). Potential participants will not be admitted to the study if they have any of the following exclusion criteria: sensory (eg, serious visual impairment), cognitive (eg, memory problems, slow processing speed, a lack of attention, linguistic problems) or physical impairment (eg, severe cognitive impairment or impairment in vision, severe astigmatism, hemiplegia, disorder in visuospatial perception, dysfunction of the central vestibular system), which may restrict the use of computers or computer game control system unaided; apathy identified in previous neuropsychological evaluations; a diagnosis of a severe mental disorder (eg, schizophrenia or severe depressive disorders to be identified as the secondary diagnosis); or having been active in cognitive rehabilitation during the previous 3 months. The primary source to assess patient eligibility will be the university hospital electronic medical records and later telephone calls and interviews with a trained psychologist.

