## Discussion

### Outcomes

The specific outcomes, such as primary outcome measures (The Trail Making Test, parts of the Wechsler Adult Intelligence Scale, 4th Edition, or WAIS-IV) were selected because they are widely used psychological tests [39,42]. They were thought to be sensitive to changes in the cognitive functions typically related to TBI. Moreover, these functions were assumed to be trained by the video games. The Trail Making Test is one of the most used neuropsychological tests globally, allowing comparisons to previous studies on TBI and rehabilitation. WAIS-IV tasks also are among the most used psychological tests in the world, and they are sensitive enough to discriminate even healthy adults. WAIS-IV has been standardized also in Finland - the home country of the participants - allowing us to compare our sample to national standards. The secondary outcome measures were selected so that a comprehensive picture of the potential changes in cognitive functions that can be assumed to be trained by the games (both the video games and the cognitive training game) is obtained. Moreover, we thought it is important to record changes in mood and self-efficacy as these influence daily life of a patient. Finally, for practical purposes it is important to gain knowledge of the feasibility of the games, as measured by adherence to the treatment and the participants’ personal experience with the game.

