#### Primary Outcome

##### Processing Speed and Visuomotor Tasks

*The Trail Making Test (TMT)* requires visual search, scanning, speed of processing, mental flexibility, and executive functions [39]. The test consists of two parts. In the first part, patients are given a paper displaying circles numbered 1 to 5 in random order. The patient is told to draw lines that will connect the numbers in ascending order. In the second part, there are circles with numbers from 1 to 13 and letters from A to L. This time, the patient draws lines to connect the circles so that they alter between numbers and letters in an ascending order (for example: 1-A-2-B-3-C) and so on. The time it takes to complete the trail is measured in both parts of the test. Errors do not affect the final score, but they must be corrected by the patient [40,41].
*WAIS-IV tasks* (symbol search, coding and cancellation*)* are a test package used to measure cognitive skills of adult patients, especially skills of sorting out simple visual information, monitoring, making progress in the task, maintaining attention, visuomotor co-ordination and visual memory [42]. The tasks constitute 4 indices that measure different areas of cognitive skills. In symbol search and cancellation tasks, the participants perform a visual search in order to find out if a certain symbol is in the midst of other symbols. In the symbol search task, the symbols are organized in rows, and the participant has to indicate whether or not the required symbol was on each row. In the cancellation task, the participant looks for the same symbols during the whole task. In the coding task, the participant is given a set of numbers and symbols that match each other. Their task is to fill out an empty grid containing only numbers with the appropriate symbols matching those numbers. The test-retest reliabilities of the tasks used in this study ranged from 0.78 to 0.86 over an 8-82 day period in the original WAIS-IV standardization study [42]. A version of the test [42] containing norms for the Finnish population is used in this study.

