#### Time for the Data Collection and Follow-Up

Patient data will be collected at three different times: at baseline, after the intervention (8 weeks), and as a follow-up, 3 months after the intervention. If required by the participant, he or she will receive a text message about 2 days before the meeting to remind them of the coming follow-up meeting.

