#### Sample Size

The calculations for the sample size needed in each group are preliminary estimations to guide our data collection, which are based on previous studies: (1) TMT (version A) and (2) depression (PHQ-9). First, if a score on the TMT version will be about 71, the mean change in the scores during the follow-up will be 30, and standard deviation of the TMT scores will be 53 [41]. This difference between groups could be expected to be significant (with a power of 85%, *p*=.05) if the sample size in each group is 30 subjects. Second, if the average level of the PHQ-9 score is about 10, the mean change in the scores during the follow-up is then 3 (SD 5) [48]. The difference could be expected to be significant (with a power of 85%, *p*=.05) if the sample size in each group is 27 subjects. Thus, based on these preliminary power calculations, the sample size to be used in this study (30 in each group) is not very strong but will be reasonable for a feasibility study aiming to detect preliminary changes within the group, between baseline and follow-up outcome measurements. However, this means that the attrition rate of the study should be near 0%. The outcomes of this study will be used as a guide to estimate a sample size for a multi-center study to be conducted, hopefully in the future.

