#### Analysis Plan

All the participants will be analyzed at the baseline, after 8 weeks when the intervention has been finalized, and at 3 months, using all the scales for primary and secondary outcomes. Comparisons in possible differences between means in 3 intervention groups and 3 time points will be conducted using analysis of variance (ANOVA test). Possible post hoc tests may be performed using paired *t*-tests, or Chi square tests to detect significant differences before and after treatment in sub-groups, if needed. Further, significant differences between groups will be evaluated applying the unpaired Student’s *t*-test using the conventional 95% level of confidence. Statistical analyses will be done using SAS System for Windows, version 9.4 (SAS Institute Inc.). *P* values less than 0.05 will be considered statistically significant.

The cumulative monitoring data during the 8-week period regarding gaming for the total number of received parameters (frequency, timing, time) will be calculated. Feasibility information (secondary outcomes) available for each patient will be calculated (participation/refusal rate, measurement instrument filled, drop-outs, acceptability, usability, satisfaction, willingness) and compared to the highest possible representative numbers (100% participation rate; measurement instrument filled, drop-out rate 0%, acceptability 100%, usability 100%, satisfaction 100%, willingness to use games in the future 100%).

Criteria for feasibility are as follows:

Willingness to participate 80% (refusal rate 20%)We expect that more than 75% of the prescheduled measurements will be performed (adherence).Less than 25% of participants drop out for to any reason (adherence)The acceptability of the game use is at least 95% (in intervention and control groups) (adherence).Usability evaluation for the gaming system is at least 80% (1 item; dichotomous scale yes/no) (usability).More than 80% are satisfied with the games (1 item; dichotomous scale, yes/no) (satisfaction)We expect that 60% are willing to use the games later as part of their recovery process (use in the future).

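### Five unranked primary measures and a blanket p<0.05 rule across three arms and two follow-up visits leave the false-positive risk on a primary outcome well above 5%

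*Protocol article*

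**What the plan says.** **Primary measures.** The Outcomes section of the Protocol article refers to "primary outcome measures (The Trail Making Test, parts of the Wechsler Adult Intelligence Scale, 4th Edition, or WAIS-IV" in the plural. Under Primary Outcome, the TMT contributes two times, since "The time it takes to complete the trail is measured in both parts of the test". WAIS-IV contributes three tasks: "symbol search, coding and cancellation". That makes five measures, none of them singled out.

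**Arms and visits.** Participants go to "one of the three parallel groups, initially in a 1:1:1 ratio", which gives three pairwise contrasts. Data are collected "at baseline, after the intervention (8 weeks), and as a follow-up, 3 months after the intervention", which gives two post-baseline visits.

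**Tests.** The Analysis Plan starts with an ANOVA over three groups and three time points, using every primary and secondary scale. It then allows paired t-tests or chi-square tests as possible post hoc work. A separate sentence adds unpaired t-tests between groups "using the conventional 95% level of confidence". It closes with the rule that P "values less than 0.05 will be considered statistically significant".

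**Sample size.** The calculations rest on "1) TMT (version A) and (2) depression (PHQ-9"). Only the first is a primary measure; PHQ-9 is listed under Secondary Outcomes.

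**The concern.** Two things that the article does state combine badly. It gives five measures equal primary status, and it gives every test the same unadjusted threshold. A report that follows the plan could therefore claim a significant effect on a primary outcome from whichever measure, contrast or visit falls below 0.05, and a reader would take that claim to carry a 5% error risk. The sample-size section does not settle which measure leads, because it pairs one primary measure with one secondary measure. Estimates picked out because they reached significance also tend to be too large, which matters when a feasibility trial is read as evidence of effect.

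**Working it through.** **1. The plan's own figure.** The Sample Size section gives 30 per group for TMT-A (change 30, SD 53, 85% power, p=.05). A paired or one-sample t-test at two-sided 0.05 gives n = 30.0, so the figure reproduces as a within-group calculation. As a two-arm comparison the same inputs need 57 per group. With 30 per arm, two-arm power is Φ(30/53 × √(30/2) − 1.96) = Φ(2.19 − 1.96) ≈ 59% (58% with the t distribution). The document gives no family-wise error rate to reproduce.

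**2. Number of tests.** 5 measures × 3 contrasts × 2 follow-up visits = 30 possible between-arm t-tests. Paired tests and secondary scales are not counted.

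**3. Bound under independence.** 1 − 0.95^30 = 78.5%. This is too high as an estimate, because contrasts share arms and measures and visits are correlated.

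**4. Simulation with no effect anywhere.** Three arms of 30, five equally correlated normal measures, two visits, two-sided 0.05, 20,000 trials per setting. The visit correlation of 0.8 is an assumption; it is in line with the WAIS-IV test-retest range of 0.78 to 0.86 quoted under Primary Outcome. The document gives no between-measure correlation, so a range is shown.

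| Reading of the plan | ρ = 0.3 | ρ = 0.5 | ρ = 0.7 |
|---|---|---|---|
| Any of 30 free-standing t-tests | 61% | 55% | 46% |
| t-test counted only after a significant ANOVA for that measure and visit | 32% | 28% | 24% |
| Any of five omnibus ANOVAs at one visit | 21% | 19% | 15% |
| Five measures, one contrast, one visit | 21% | 18% | 15% |

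Repeat runs differ by a point or two, so the second row is best read as about 23–33%. For five independent tests the ceiling is 1 − 0.95^5 = 22.6%.

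**5. Sensitivity.** With both correlations varied from 0 to 0.9, the first row runs from 31% to 73%.

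**6. After the change.** One pre-named measure, contrast and visit has a risk of 5%. Holm adjustment over the five measures, for one contrast at one visit, starts at 0.05/5 = 0.01 and keeps the risk at or below 5% (simulated 4.7%, 4.3% and 3.3% for ρ = 0.3, 0.5 and 0.7).

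**The case against.** **The ANOVA comes first.** This is the strongest objection, and much of it stands. A reader who counts 30 t-tests might infer that a false positive is about as likely as not. The document does not support that as the only reading. It puts the three-group by three-time ANOVA first, and it never says that every pair will be tested on every measure at every visit. Thirty is a ceiling, and 46–61% is the upper reading.

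Even so, the unpaired t-tests sit in their own sentence, outside the one on post hoc tests, and nothing makes them conditional on the ANOVA. A gate also would not bring the risk to 5% while five measures remain equal. The kindest reading admits t-tests on follow-up scores only after a significant group-by-time interaction, and then the t-tests alone carry about 6–8%. But the threshold applies to any P value, and the chance that at least one of the five interactions is itself significant is about 16–22%.

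**It is a feasibility study.** The numeric success criteria concern participation, dropout, usability and similar measures, and none uses an efficacy p-value. This lowers the weight of the point and makes an exploratory label a reasonable remedy for most results. It does not remove the point, because the aim includes evaluating effects and the plan declares significance on primary measures.

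**An analysis plan may exist.** Missing adjustment detail alone would be no finding in a condensed article. The point here rests on what the article does state: several unranked primary measures and one blanket threshold.

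**The multi-centre trial.** A reader might infer that effects selected for significance will size the later study. The Sample Size section says only that outcomes will guide that estimate. Standard deviations and attrition are equally possible inputs.

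**Conclusion.** The concern holds, with its size depending on how the tests are chained. Under the three readings taken here, the risk of at least one false claim on a primary measure is about 46–61% with free-standing t-tests, about 23–33% with an ANOVA gate per measure and visit, and about 15–21% with five omnibus tests at one visit. The counts, the threshold and 30 per arm come from the document. The between-measure correlation (0.3–0.7), the visit correlation (0.8) and normal data are assumptions. The risk is therefore roughly three to twelve times the nominal 5% (15/5 = 3; 61/5 ≈ 12). The feasibility setting makes this something that should be corrected rather than a fatal flaw.

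**What to change.** Before the data are analysed by arm, name one primary measure, one contrast and one visit, tested at two-sided 0.05. TMT-A is the natural measure, as the only primary measure used for the sample size. No passage ranks the contrasts or visits, so the sponsor should choose those. Alternatively, keep all five measures and apply Holm adjustment across them, with the contrast and visit still fixed in advance. Report all other measures, contrasts and visits as estimates with 95% confidence intervals, labelled exploratory. Replace the blanket 0.05 sentence with wording that limits claims of significance to the primary test or the Holm family.

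The edit is a few sentences, but it has costs:

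- Fewer results can be called significant.
- The article reports recruitment as finished, and participants and Research Assistants are not masked. The change must therefore be dated and documented as made after recruitment ended. The Randomization section keeps the trial statistician blinded, which makes a change before analysis by arm credible.
- A single between-arm TMT-A test has only about 59% power at 30 per arm (difference 30, SD 53). At Holm's first step of 0.01 the same calculation gives Φ(2.19 − 2.58) ≈ 35%. The plan should state the power of whichever option is chosen.

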#### Ethical Issues

A proposal for this study has been evaluated by the ethical committee of the Turku University Hospital (ETMK 41/1801/2015). The permission to conduct the study has been granted by the Turku University Hospital (T89/T04/008/2015). The trial has been officially registered (NCT02425527). All patients will be informed of the study orally and in written format. Informed consent will be obtained for experimentation with human subjects. The neurologist is a part of the study group and an expert in this kind of treatment. Study participation is completely voluntary (a signed informed consent, the Declaration of Helsinki 2013).

Possible ethical issues have already been taken into account in the development phase of the study: the rehabilitation and entertainment games were pre-tested with five healthy adults and with five people with TBI. Based on pre-tests, it was possible to identify more specific inclusion and exclusion criteria for the study. In addition, specific games were identified and excluded, (eg, those which may cause dizziness or headaches in participants due to dark colors, 3D tunnel effects, and so on) [51].

Study participants will have full understanding of the content and purposes of the study. They will be informed orally a total of 3 times before their informed consent is asked for (2 telephone calls, 1 face-to-face meeting). Written consent to participate in the study will be requested from participants after they have been informed of all aspects of the study. According to the Finnish Medical Research Act (488/1999) [52] the participants will be informed that in case they withdraw from the study for any reason, their information that has already been collected will not be removed from the research material. Participants will have no obligation to provide information they do not want to share. They can also withdraw from the study at any time without providing a reason. Refusal to participate in the study will not have any effects on their daily lives. Further, the psychological safety and emotional stability of the responders also will be taken into account. They will be free to stop answering questionnaires at any time, in case they feel uncomfortable or distressed. If a participant would like to have additional information, they will be informed about a contact person who can answer their questions by telephone, email or text messaging.

To shorten the first face-to-face meeting with the Research Assistant, participants will receive paper-format questionnaires by post. For follow-up interviews (after the 8-week intervention and 3-month period) participants will return the filled questionnaires in a pre-paid envelope or during their face-to-face meeting with the Research Assistant. The participants in the “as usual” group will return the filled-in questionnaires by post only. The participants will not be charged for any costs associated with data collection. Participants will be informed that if the console breaks down, they are not liable for damages. In special cases, the Technical Assistant will visit the participant’s home to repair devices if needed. If any technological problems arise during the intervention, the participants have the opportunity to contact the Technical Assistant by phone or email to receive practical or hands-on support.

The privacy rights of human subjects will be observed at all times. Respondents’ answers will not be provided to organizations outside the study. Information obtained will be used only for its original purpose. Information derived from research data will be coded and recorded in such a way that subjects cannot be identified [53]. All collected data will be transferred, recorded and securely stored (Personal Data Act 523/1999, Archive Act 831/1994, Constitutional Act 731/1999) [54-56].

The participants in the group assigned entertainment gaming may choose games targeted for an audience of young adolescents or 16 years old or younger. All participants in intervention groups can change the game during the intervention period if they find the game to be unpleasant, boring or otherwise dissatisfying. Moreover, all participants will be adults (over 18 years) who are capable of playing the games if they are willing to do so. The games being used are commercially available; however, some are designed only for adult players. These action games may include explicit graphic content, emotionally challenging themes or rough language. We found studies related to possible outcomes of playing this type of action game: some studies concluded that action games with violent elements may cause negative outcomes with aggression [57,58]. Contrasting results have also been found: it has been concluded, for example, that action games do not lead to aggressive behavior in adult users [59]. Regarding the potential positive effects of the games, they are associated with higher visuospatial cognition or visual skills [59]. Non-violent games do not appear to generalize to visuospatial cognitive abilities even when they involve visual rotation tasks [60].

The study will be conducted in accordance with the Finnish Medical Research Act (488/1999, amended 295/2004) [54], and Amendments (295/2004); Personal Data Act (523/1999) [54]; the Act on the Openness of Government Activities (621/1999). The principles of research ethics will be followed [61,62]. Any regulations addressing the conduct of a vulnerable population will be taken into account. This population could not be reached in another data collection method (eg, a register study).

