
Third, the participants in the passive control group will not have gaming activities organized by the project. As with the intervention groups, the Research Assistant will call weekly to the participants in this study arm. In addition, as patients in a control group, these participants will be offered an opportunity to have games and consoles for a 2 week period free of charge after the study. Further, 5 out of the 90 participants will have a chance to randomly win a console to keep after the study intervention period.

The procedure for patient recruitment and allocation will consist of specific steps. First, potentially eligible participants will be selected from the hospital patient records based on the inclusion criteria with the help of a specialist in neurology. Those patients who have been screened and assessed a prior to meet the inclusion criteria will be contacted by telephone by the Research Assistant. Any cognitive and physical problems limiting patients’ ability to participate in the study will be discussed by phone. If a patient cannot be reached by the telephone call, a written information letter about the study will be posted to him or her. If interested, he or she can contact to the Research Assistant. A preliminary description of the study will be offered, and the inclusion criteria for the study will be described to the potential participants. Based on the discussion with the participants, their eligibility for the study will be decided. Eligible participants will also be asked about preliminary interest in the study. They will be informed that they will receive information about the study by post, 2 informed consent forms, questionnaires to be filled in (baseline data), and a short description of the 8 optional games (in case of allocation to the control group).

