#### Randomization

The study will be individually randomized. The randomization and patient allocation will be fully centralized. A central randomization service provided by the University of Turku will be used. Allocation will be computer generated. The participants will be randomly assigned (a block randomization in three blocks) using numbers via computerized assignment developed by the independent trial statistician and implemented by the Research Assistants (2), who are trained in patient randomization and data collection.

The research assistants overseeing patient recruitment and randomization will be aware of the assignments. Allocation will not be masked to participants in intervention and control groups or Research Assistants who will recruit patients. The psychologists, as cognitive outcome assessors, will be masked. The data analyst (the trial statistician) will be kept blinded to the allocation. As far as we are aware, there will be no contact between participants in different groups; participants will come from a wide geographic area in the catchment area of the Southwest Hospital District in Finland.

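### Follow-up questionnaires may be posted or handed over in the gaming arms but only posted in the passive control arm, an avoidable risk of arm-dependent non-return on the self-report scales

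*Protocol article*

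**What the plan says.** All statements are in the protocol article.

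- **General rule (Ethical Issues).** For the interviews after the 8-week intervention and at 3 months, "participants will return the filled questionnaires in a pre-paid envelope or during their face-to-face meeting with the Research Assistant".
- **Exception (Ethical Issues).** The 'as usual' "group will return the filled-in questionnaires by post only". The label is not defined and is used for no arm elsewhere. Under Interventions, "the participants in the passive control group will not have gaming activities organized by the project", and the other two arms both play games, so the label can only mean the passive control arm.
- **Baseline (Ethical Issues).** "participants will receive paper-format questionnaires by post", with no difference by arm.
- **Masking (Randomization).** "The research assistants overseeing patient recruitment and randomization will be aware of the assignments". Participants are not masked either: "Allocation will not be masked to participants in intervention and control groups or Research Assistants who will recruit patients". For the cognitive tests, "The psychologists, as cognitive outcome assessors, will be masked".
- **Use of the data (Analysis Plan).** "All the participants will be analyzed at the baseline, after 8 weeks when the intervention has been finalized, and at 3 months", on every primary and secondary scale, with comparisons across three groups and three times.
- **Scales concerned.** PHQ-9 (Depression), the General Self-efficacy Scale (Self-Efficacy) and BRIEF-A (Executive Functions) are completed by the participant and are secondary outcomes. PHQ-9 is also one of the two outcomes used under Sample Size.

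**The concern.** Allocation decides which return routes are open. A gaming participant who has not posted the form can still bring it to the meeting, where a gap can be noticed. A passive control participant has no such second chance under the rule as written. If return or completeness then differs by arm, the observed contrast on these scales mixes any treatment effect with selection of who returned a form. The planned ANOVA and t-tests do not separate the two.

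There is little slack. The Sample Size section says attrition should be close to zero and gives 27 per group for PHQ-9 against 30 planned. Return below 27/30 = 90% in an arm is therefore already under the protocol's own number. Completion of instruments is itself a feasibility measure meant to inform a later multi-center trial, and a harder route in one arm would distort it.

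**Working it through.** **1. The plan's own PHQ-9 figure.** Inputs (Sample Size): change 3, SD 5, power 85%, p = .05, 27 per group.

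- Paired (one-sample) test, two-sided, normal approximation: n = ((1.960 + 1.036) × 5/3)² ≈ 24.9. With the t distribution n = 26.9, so 27, which matches.
- Two-sample t-test for a difference of 3 between arms: n = 50.9, so 51 per group, which does not match.

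The 3 points therefore act as a change within a group. They are not a planned difference between arms.

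**2. Bias from unequal return.** The documents give no return rates, so these inputs are assumptions:

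- share missing in a gaming arm: 5%;
- share missing in the passive arm: m, from 10% to 40%;
- non-returners differ from returners by g SD, with g = 0.5 or 0.8, the same in both arms;
- SD = 5, from Sample Size.

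Within an arm, the mean of returners differs from the mean of all participants by (share missing) × g × SD. The between-arm bias is the difference of these two terms:

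bias = (m − 0.05) × g × 5

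| m (passive arm) | g = 0.5 | g = 0.8 |
|---|---|---|
| 5% (equal return) | 0 | 0 |
| 10% | 0.12 | 0.20 |
| 20% | 0.38 | 0.60 |
| 25% | 0.50 | 0.80 |
| 40% | 0.88 | 1.40 |

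Example: (0.40 − 0.05) × 0.8 × 5 = 1.40 points. The direction is unknown. If non-returners are more depressed, the passive arm looks better than it is and a benefit of gaming is understated. If they are less depressed, a benefit is overstated.

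**3. Loss of precision.** Take a between-arm difference of 3 (SD 5) purely for illustration. Two-sample t-test power is 62.8% at 30 per arm, 60.5% with 5% missing in both arms, 56.5% with 20% missing in the passive arm and 49.6% with 40%.

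**4. Would the feasibility criteria reveal it?** They expect more than 75% of scheduled measurements and under 25% dropout, and neither is set by arm. Read as pooled, 5%, 5% and 40% missing questionnaires average (5 + 5 + 40)/3 = 16.7%, so 83.3% are returned. A marked imbalance could pass unnoticed.

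**The case against.** The strongest reply is that only the return of the form differs. All arms complete the same paper questionnaires themselves, and gaming participants may also post theirs, so the routes overlap. Participants know their arm whatever the route, so self-report bias exists anyway and handing over a completed form probably adds little. The weekly Research Assistant calls also go to the passive arm and may prompt return at 8 weeks. These are secondary outcomes in a declared feasibility study.

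Most of this stands, and it is why the reporting-bias part is minor. It does not remove the non-return part. The passive arm still has fewer ways to return a form, and the weekly calls are not clearly stated to continue to the 3-month follow-up.

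A reader might also infer that passive controls have no follow-up visit, so that TMT and the WAIS-IV tasks would be missing for the whole arm. The documents do not support this. The post-only sentence concerns questionnaires and says nothing about attendance. The section on the time of data collection sets three occasions, refers to a follow-up meeting and exempts no arm, and the Analysis Plan includes all participants on all scales. The wording is awkward and deserves a clarifying sentence, but it does not show missing primary data.

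**Conclusion.** The point holds as a risk that the stated procedure creates without need. It concerns PHQ-9, self-efficacy and BRIEF-A at both follow-ups, and only comparisons with the passive control arm. The two gaming arms share the same rule. The cognitive tests are given by masked psychologists and do not depend on how questionnaires come back.

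Under the assumed missing rates and non-returner differences, the PHQ-9 bias ranges from about 0.1 to 1.4 points. It is zero if return is equal in all arms. The two limbs differ in strength: unequal return is the substantive one, and added reporting bias from hand-over is probably modest.

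Two stronger readings go too far. One is that bias is already built into these scales: the text shows unequal opportunity to return a form, not unequal return. The other is to express a route effect as a share of a planned 3-point difference between arms. The article describes 3 points as a change during follow-up, its n of 27 reproduces only as a within-group test, and no passage supports a particular size of route effect.

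**What to change.** 1. Delete the post-only sentence. Offer the same return options and the same reminder procedure in all three arms at 8 weeks and 3 months.
2. Have forms handed over in a sealed envelope, or received by someone who does not know the allocation.
3. Report questionnaire return by arm at each follow-up.
4. Replace the undefined 'as usual' label with passive control group, and state that this arm attends the same 8-week and 3-month test visits, as the data-collection and analysis sections imply.

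The cost is a small change in procedure wording and in the handling of forms. No visit is added, because the cognitive tests already require one in every arm. If the sponsor has a reason for the post-only rule, it should be stated.
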